#### **4.5.1.3 Serious incident**

A serious incident is defined as any adverse event or side effect that either

- Leads to death, or
- is life-threatening, or
- Leads to a permanent or serious disability or invalidity, or
- Requires inpatient treatment or its prolongation (unless the inpatient treatment was already planned before participation in this study).

Depending on the causality to the study intervention, a distinction is made between a serious adverse event (SUE) or a serious adverse reaction (SNW).

#### **4.5.1.4 Severity**

The severity levels of the incidents ((S)UE and (S)NW) are defined as follows:

- Mild - Intervention must be interrupted due to the incident, but can be continued the same day or the following day. Consultation with a doctor for treatment is not necessary;
- Moderate - Intervention must be interrupted, can be continued on another day but not immediately the following day. Consultation with a doctor for treatment is necessary.
- Severe - The intervention must be terminated and cannot be continued due to the event (in terms of a drop-out according to chapter 5.4)

#### **4.5.1.5 Causality**

Causality is defined as follows:

- Treatment-associated - Either the adverse event is known to be caused by the study intervention, or there is reasonable suspicion that the study intervention caused the adverse event, or there is a temporal relationship between the study intervention and the occurrence of the adverse event.
- Non-therapy associated - There is no reasonable suspicion that the adverse event was caused by the study intervention or there is no temporal relationship between the study intervention and the occurrence of the adverse event.

## **4.5.2 Assessment and documentation**

Within the framework of this study, all adverse events and side effects are systematically recorded, assessed and evaluated at the end of the study.

### **4.5.2.1.1 Assessment process**

An authorised doctor must evaluate and confirm the possible association with the intervention, the severity (mild, moderate, severe) and the classification of the incident as serious or non-serious.

### **4.5.2.1.2 Documentation of adverse events (UE/NW)**

During the intervention phase (week 1 - week 4), the occurrence of the above-mentioned incidents will be recorded by the responsible staff at the study centre and assessed by a member of the medical team.

All incidents and findings must be documented in the patient record and subsequently in the UE log of the CRF.

The following information is required:

- Type of Adverse Event (sign, symptom or disease)
- Beginning and end of occurrence
- Severity
- Causality to intervention
- Differentiation (serious/not serious)
- Measures regarding the intervention or actions to restore or improve the patient's well-being.
- Outcome of the event.

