#### Patient-related:

Active intervention duration: 4 weeks

After inclusion, the duration of each participant's participation will be 8 weeks (baseline survey, 4-week intervention, post-intervention testing, focus group for intervention group 1 participants only, follow-up call 4 weeks after the end of the intervention). The total duration of the study will be 8 months.

Figure 1 presents the patient-related study process.

[figure not shown]

**Figure 1:** Patient-related study procedure

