### 4.2 Intervention

#### 4.2.1 Treatment scheme

The study includes a screening, a baseline examination, 16 intervention sessions a' 30 min over 4 weeks, a post-intervention testing, a focus group for the participants of the intervention group and a follow-up call 4 weeks after the end of the intervention.

The duration and number of examinations and treatments (Table 1) will take place in the context of the patients' inpatient interdisciplinary rehabilitation. It is ensured that all study participants receive the same number of treatments in total. In addition, all participants must receive 8 30-min sessions of physiotherapy per week, of which 4 are reserved for the study intervention in group 1 or 2 and represent an additional measure. All therapists will be trained on the study interventions and instructions for participants in both groups and will therefore work according to the same principles.

**Table 1:** Treatment regimen of a (screened possible\*) study participant

| Intervention                | Dosage | Time                                                                      | Duration    |
|-----------------------------|--------|---------------------------------------------------------------------------|-------------|
| Screening*                  | 1x     | After verification of suitability by the investigator and patient consent | 10-15 min   |
| Study inclusion             |        |                                                                           |             |
| Baseline investigation      | 1x     | Day 0 after study inclusion                                               | 75-90 min   |
| Intervention groups 1 and 2 | 16x    | Start on day 1 after the baseline examination                             | 30 min each |

|                          |    |                                                                                                                                           |           |
|--------------------------|----|-------------------------------------------------------------------------------------------------------------------------------------------|-----------|
|                          |    | 4 x per week, 4 weeks in total                                                                                                            |           |

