| Depression                                                                                                                               | Beck Depression Inventory-II (BDI-II)                                                                                     |  | X |   | X |   |
| Fall rate                                                                                                                                | Number of falls (a) in the 3-month period before study entry (BL), (b) intervention period (PI) and (c) 4-week follow-up. |  | X |   | X | X |
| Feasibility of a larger randomised controlled trial                                                                                      |                                                                                                                           |  |   |   |   |   |
|                                                                                                                                          | Recruitment rate                                                                                                          |  | X |   |   |   |
|                                                                                                                                          | Retention rate                                                                                                            |  |   |   | X | X |
|                                                                                                                                          | Adherence rate                                                                                                            |  |   | X |   |   |
|                                                                                                                                          | Adverse events                                                                                                            |  |   | X | X |   |
|                                                                                                                                          | Acceptance of the intervention (continuous: narrative; focus groups in intervention group 1)                              |  |   | X | X |   |

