### **4.5 Adverse events, side effects**

#### **4.5.1 Definitions**

The implementation of the tests and interventions (therapy of the intervention groups) can trigger adverse events and side effects. During the therapy, events such as dizziness, shortness of breath or similar signs of stress may occur as a physiological reaction to stress (the training) in both the intervention group and the control group. In the intervention group, slight eye fatigue may occur, but this can be well controlled by short training sequences, variable exercises as well as breaks and exercises without eye movement training.

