#### **4.5.1.1 Adverse event (AE)**

An adverse event (AE) is any adverse occurrence that happens to a subject during participation in this study that is not necessarily causally related to the intervention. This may include illnesses, signs and symptoms that occur after the subject is included in this study or pre-existing illnesses, signs and symptoms that worsen after inclusion in this study.

Pre-existing conditions that do not worsen during the course of the study and adverse events related to concomitant medication are excluded.

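### Non-serious adverse events have no scheduled recording at the day-0 baseline test or in the 4-week follow-up, although the protocol defines adverse events over the whole 8-week participation

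*Protocol*

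**What the plan says.** Five places in the protocol bear on the window for adverse events.

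- **Definition.** Section 4.5.1.1 covers "any adverse occurrence that happens to a subject during participation in this study". Section 3.5 adds: "After inclusion, the duration of each participant's participation will be 8 weeks".
- **General promise.** Section 4.5.2 states that "all adverse events and side effects are systematically recorded, assessed and evaluated at the end of the study", with no time limit.
- **Instruction to staff.** Section 4.5.2.1.2 reads: "During the intervention phase (week 1 - week 4), the occurrence of the above-mentioned incidents will be recorded by the responsible staff". The entries go to the adverse-event log in the case report form, and severity is one of the required items.
- **Visit schedule.** In Table 2 (section 4.3.3) the row "Adverse events" is marked for the intervention period and the post-intervention visit. The columns for baseline and the follow-up call are empty.
- **Source of events.** Section 4.5.1 says: "The implementation of the tests and interventions (therapy of the intervention groups) can trigger adverse events and side effects". Tests are thus named beside training as a possible cause.

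Table 1 (section 4.2.1) places the baseline test at "Day 0 after study inclusion" and the first training session on day 1.

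**The concern.** The definition and the general promise cover 8 weeks. The operative instruction and the visit table cover the training period plus one visit. Staff at the centre will work from the instruction and the table, so two periods have no planned entry for non-serious events.

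The first is the baseline test. Section 4.3.3.1.1 has the glasses worn at all assessments and warns of temporary dizziness. The baseline test is the first occasion on which they are worn.

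The second is the month after training. Section 4.3.2 gives the follow-up call a short interview, a falls question and two questionnaires, and names no adverse-event enquiry.

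What is at stake is the safety part of the feasibility decision. Criterion (d) in section 4.4.14.1 is judged from a log described as continuous, and the larger trial will inherit both the test procedure and the safety statement.

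**Working it through.** No stated figure has to be reproduced; the check sets the windows side by side.

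**Inputs.** Participation is 8 weeks (section 3.5). Baseline is on day 0, training starts on day 1 and lasts 4 weeks, and the follow-up call comes 4 weeks after training ends (Table 1). Planned enrolment is 34, 17 per group (section 4.1.2.3).

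**Windows in days.**
- Definition: day 0 to about day 8 × 7 = 56.
- Recording under section 4.5.2.1.2: days 1 to 4 × 7 = 28.
- Table 2 adds the post-intervention visit at the end of that span.
- Without scheduled recording: day 0, and from after the post-intervention visit to about day 56.

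**Glasses.** Section 4.3.3.1.3 gives about 5 minutes of wear at baseline and at post-intervention, and 12 minutes once a week during training. Table 2 lists the weekly measurement for group 1 only. On that reading:
- group 1: 1 + 4 + 1 = 6 planned occasions, of which 1 (baseline) lies outside the recording window;
- group 2: 1 + 1 = 2 planned occasions, of which 1 (baseline) lies outside.

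All 34 planned first exposures are outside the window.

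**What other rules cover.**
- Serious incidents: section 4.5.3.1 requires reporting throughout the study once they are known, and section 4.5.2.1.3 requires them in the log as well as on the separate form. Section 6.4 obliges patients to report emergency treatment, and study-related damage to health, without being asked.
- Falls in follow-up: Table 2 and section 4.4.13(c) collect them at the call. Section 4.3.2 describes the falls question in that call as being about the intervention period, so this sentence should be aligned too.

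**What remains.** Non-serious events other than falls, on day 0 and in follow-up.

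**Can such events be graded?** Section 4.5.1.4 defines mild, moderate and severe by whether the intervention is interrupted, resumed or ended. Before day 1 and after week 4 there is no training session to interrupt. As worded, the scale does not fit events in those periods, although section 4.5.2.1.2 makes severity a required entry.

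**The case against.** The strongest reply is that recording is matched to exposure. Criterion (d) concerns the safety of the intervention. A reaction on day 0 precedes all training and cannot be an effect of it, and no study training takes place after week 4. Weeks 1-4 plus the post-intervention visit span the whole training exposure, in a study that section 1.3 regards as low risk. This stands as far as criterion (d) is read as training safety. It does not remove the mismatch with sections 4.5.1.1 and 4.5.2, and it leaves aside the safety of the tests, which section 4.5.1 itself raises.

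Second, section 4.5.2.1.2 does not say that recording happens only in weeks 1-4, section 4.5.2 sets no limit, and section 1.3 says that complaints are asked about before, during and after the intervention. The last statement may refer to each session or to the programme as a whole, and it names neither a visit nor a log entry. The fair description is an internal contradiction, not a settled rule that discards events.

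Third, the content of the short interview and the case report form are not shown. An open question may already exist there; the protocol does not say so.

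A reader might also infer that serious events after discharge would come to light only if someone asked. The documents do not support that, given the reporting duties in sections 4.5.3.1 and 6.4.

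**Conclusion.** The contradiction is real and should be resolved. Non-serious events have no scheduled recording at the baseline test or in follow-up, although the protocol defines them as adverse events and says that all are recorded.

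The size can be stated only as coverage: day 0 for all 34 planned participants, and the 4 weeks of follow-up. It is tempting to go from 34 × 4 = 136 recorded out of 34 × 8 = 272 person-weeks, or 50%, to half of the events being missed. That does not follow. The 50% is a share of time, it weights weeks without training like weeks with training, it ignores the post-intervention mark and drop-out, and events may well cluster during training. No event rate is given, so no number of missed events can be derived.

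The conclusion assumes that staff follow section 4.5.2.1.2 and Table 2, and that the case report form has no adverse-event entry for baseline or the call. Sample size and the efficacy analyses are not affected.

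**What to change.** 1. State one recording window, from study inclusion (baseline test) to the follow-up call, and use it in sections 4.5.1.1, 4.5.2, 4.5.2.1.2 and Table 2.
2. Mark adverse events at baseline and at the follow-up call in Table 2.
3. Make sure that the follow-up call contains one open adverse-event question and name it in section 4.3.2. If the case report form already has one, citing it is enough.
4. Reconcile the severity definition in section 4.5.1.4 with the wider window, so that events outside weeks 1-4 can be graded. Without this step the added records would lack a required item.
5. Report events by period (baseline test, intervention, follow-up), so that criterion (d) can still be judged on the training period alone.

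The cost is about one line in the case report form, one or two minutes in a call that already takes place, and a text change to the severity section. The drawback is less precise recall of non-serious events after discharge, and reporting by period keeps those events apart from the ones observed in the clinic.

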#### **4.5.2.1.3 Documentation of serious incidents (SUE/SNW)**

Serious incidents must be recorded in the CRF Serious Incident Report Form in addition to the documentation in the UE Log.

The following points must be strictly adhered to when documenting the serious incidents:

- Each SUE/SNW must be reported as completely as possible.
- Findings must be attached to the report in pseudonymised form (using the patient's code).

The investigator of the respective trial site must check the serious incident report form for completeness and ensure that the information entered matches that in the CRF UE log and other data sources.

### **4.5.3 Reporting of serious incidents (SUE/SNW)**

#### **4.5.3.1 Reporting obligations of the examiner**

All serious incidents occurring during the study must be reported immediately after becoming aware of them ( $\leq 24$  hours/1 working day) by submitting the Serious Incident Form to the Coordinating Investigator and Sponsor (email: [contact]).

Please note: Personal data (e.g. findings) must be pseudonymised using the patient's code before they are transmitted (DSVO-compliant: in person, analogue fax).

#### **4.5.3.2 Reporting obligations of the sponsor**

The sponsor must inform the Ethics Committee of the Medical University of Innsbruck in writing about all serious incidents that occur during the course of this clinical trial immediately after they become known ( $\leq 24$  hours/1 working day).

In the event of (unanticipated) occurrences that may lead to an increase in risk, the Ethics Committee must be referred again.

## **5 Data documentation , -management and -evaluation**

### **5.1 Data collection methods**

The data collection for the evaluation of the endpoints is exclusively collected with valid, reliable and responsive patient-oriented instruments, which are listed and described in chapter 4.4.

## 5.2 Documentation

### 5.2.1 Source data and documents

Source data is considered to be all information from original documents and reports and their certified copies that is necessary for the reconstruction and assessment of the study. Source data are contained in source documents.

Source documents in this study are:

e.g. medical records, consent forms, therapy documentation, etc.

### 5.2.2 Survey questionnaire (CRF)

All patient data and examination results will be entered into the CRFs (Case Report Forms) specially created for this study.

The survey forms may only be filled in **with a biro or fineliner (black or blue)**. Corrections must be made in such a way that the old entry remains legible (the use of correcting agents is not permitted). Corrections must be signed and dated by the authorised person making them. Data that are not available or that have not been collected must be clearly identifiable as such (F or ND). The reasons for this should be documented, if applicable.

The investigator shall ensure that all patient data are entered into the CRFs promptly, legibly, completely, accurately and in accordance with the patient records.

The completed original pages are sent to the responsible persons for data entry and evaluation of the data.

## 5.3 Further treatment of patients after completion of the examination

The patients are subject to the regular care scheme within the framework of their treatment of idiopathic Parkinson's syndrome, according to which further care is also provided after completion of the study.

## 5.4 Drop-out of patients (drop-out)

Patients may withdraw from the clinical trial at any time at their own request, early and without giving reasons and without consequences for their future treatment. In addition, patients can be excluded from the study by the investigator for reasons of health risk.

The following points or events also lead to the drop-out of the subject after initial inclusion in the study (in the sense of a classification as drop-out for the biometric analysis):

- No questionnaire scores or assessment scores of interpretable quality.
- Withdrawal of consent to study participation by the study participant within their study integration.
- Any change or adjustment in dopaminergic medication that the investigator decides is no longer compatible with the study objectives - see exclusion criteria.

If, after the start of the study intervention, the patient's health is endangered due to an unexpected deterioration in health or general condition and/or an absolute contraindication to physical training, participation in the study will be terminated immediately and a specialist consulted.

The reason for the patient's withdrawal from the study is documented in the CRF. The study must be continued with the next subject number.

All patients who leave the study prematurely are asked to undergo a final examination in the form of post-intervention testing at the next possible opportunity - if this is possible during the rehabilitation period and if they are in good health - and the results of this examination will be documented in the CRF.

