##### **4.4.9.1 Implementation and evaluation**

The PDQ-39 is a 39-item questionnaire for self-evaluation of health-related quality of life (Patient Rated Outcome Measure, PROM). It consists of 8 dimensions: Mobility (items 1 to 10, max. 40 points), daily activities (items 11 to 16, max. 24 points), emotional well-being (items 17 to 22, max. 24 points), stigma (items 23 to 26, max. 16 points), social support (items 27 to 29, max. 12 points), cognition (items 30 to 33, max. 16 points), communication (items 34 to 36, max. 12 points), physical discomfort (items 37 to 39, max. 12 points). The evaluation is based on a 5-point Likert scale, from 0 = "Never" to 4 = "Always". Recoding of the response categories is not necessary for the creation of the subscales. All 8 domain scores and the Global Index are standardised on a 0-100 scale, with 0 representing the best health-related

QoL and 100 the worst. Mapi Trust provides an SPSS syntax for scoring. The index can only be calculated in each case if the percentage of missing data for all dimensions is  $\geq 50\%$ . The PDQ-39 takes 10-20 min to complete.

The evaluation is based on the evaluation instructions for the German version of the PDQ-39 (Berger et al., 1999).

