### Missings

The handling of missing answers (missings) requires special attention. Since they cannot be avoided in self-answering, the following procedure is recommended. If at least 50 per cent of the items of a subscale have been answered, the missing answers are replaced by the mean value of the existing answers in this scale. This means that in the 10 item scale a maximum of 5 questions may remain without an answer, in the 6 item scales a maximum of 3, in the 4 item scales a maximum of 2 and in the 3 item scales only one question. After replacing the missing answers with the mean values of the existing ones within a subscale, the sum scores of the eight subscales are calculated by addition and transformation as described above. When collecting the PDQ answers in the interview, no missings should occur.

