## 5.6 Data analysis

### 5.6.1 Statistical data analysis

Statistical data analysis is performed using IBM SPSS software, version 26.0 (IBM Corporation, Armonk, NY, USA) and Tobii Pro Lab Analyser (Tobii, Danderyd, Sweden). The statistical significance level is defined by a p-value of  $<0.05$ . An attempt is made to avoid missing data by inspecting the questionnaires after completion and, in case of unanswered items, asking the study participants to complete them. The number of missing data is noted; due to the less sensitive topic of the study, it is assumed that missing variable values can be assigned to "missing completely at random" or "missing at random". An intention-to-treat analysis is performed for all cases analysed in their originally assigned group.

Descriptive statistics are used for demographic data and primary and secondary outcomes. Counted and nominal scaled data (gender, fall rate, recruitment, retention and adherence rate, number of missing data if applicable, number of adverse events) are reported as whole numbers or percentages. Ordinal scaled variables (MMSE, UPDRS, H & Y, FGA, BBS, PDQ-39, FOGQ, FES-I, BDI-II) are expressed as median (minimum, maximum or interquartile range) and metric variables (TUG, TUGman, FSST, 10MWT, eye movements: Saccade velocity, amplitude, latency, fixation duration) by mean (95% confidence interval, CI or standard deviation, SD). The data is also presented graphically (e.g. by bar charts, box plot or line graphs).

The eligibility rate (%) is the percentage of patients suitable for the study after applying the inclusion and exclusion criteria from the Parkinson's patients treated at the Reha Zentrum Münster during the study period.

The recruitment rate (%) is determined as follows:  $(N_{\text{Consent}}/N_{\text{eligible}}) \times 100$ ; where  $N_{\text{Consent}}$  is the number of participants who signed the informed consent form;  $N_{\text{eligible}}$  is the number of patients eligible for the study based on the inclusion and exclusion criteria.

The retention rate (%) is calculated as follows:  $(N_{\text{completed}}/N_{\text{Total}}) \times 100$ ; where  $N_{\text{completed}}$  is the number of participants who completed the study;  $N_{\text{Total}}$  is the total number of participants in the study.

Adherence rate (%) is determined as follows: (Actual number of exercise sessions/planned number of training sessions)\*100 (Osterberg & Blaschke, 2005).

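### The drop-out rule in 5.4 is not reconciled with the intention-to-treat promise in 5.6.1; separately, the PDQ-39 index condition in 4.4.9.1 is reversed

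*Protocol*

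**What the plan says.** **Analysis set.** Protocol 5.6.1 states: "An intention-to-treat analysis is performed for all cases analysed in their originally assigned group". Protocol 5.4 lists three events after inclusion that make a patient a drop-out, "in the sense of a classification as drop-out for the biometric analysis". The first is that the patient has no usable scores, and the second is that the patient withdraws consent. The third rests on a judgement: "Any change or adjustment in dopaminergic medication that the investigator decides is no longer compatible with the study objectives".

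The same section also provides for outcome data from these patients: "All patients who leave the study prematurely are asked to undergo a final examination in the form of post-intervention testing". That examination depends on the patient still being in rehabilitation and in good health. Protocol 6.5 keeps data stored before a withdrawal of consent in use, as far as they are needed to determine the effects of the intervention.

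**PDQ-39.** Protocol 4.4.9.1 says of the summary index: "The index can only be calculated in each case if the percentage of missing data for all dimensions is" at least 50%. The Missings paragraph that follows in 4.4.9 sets the subscale rule: "If at least 50 per cent of the items of a subscale have been answered", the gaps are filled with the mean of the answered items. It allows at most 5, 3, 2 and 1 unanswered items in scales of 10, 6, 4 and 3 items.

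**The concern.** The label in 5.4 is tied to the analysis, not only to participation, and no section says that a patient who carries it is still analysed in the assigned arm. The medication trigger is the one that matters most. It is a discretionary judgement made after randomisation, it is likely to follow the course of the disease, and it can fall on a patient who has both a baseline and a final FGA. If such patients are left out, the groups compared are no longer the groups that were randomised. The protocol uses between-group mean differences and SDs from this pilot to size the later trial (5.6.1), so a distorted contrast would carry forward.

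The PDQ-39 point is a separate matter of scoring. Taken literally, the index exists only for patients who left large parts of the questionnaire blank.

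**Working it through.** **1. Inputs.** Thirty participants, a 10% failure rate, 34 in total and 17 per arm (4.1.2.3); a retention target of 80% (4.4.14.1); an FGA minimum detectable change of 4 points (4.4.1.2). FGA is listed as ordinal and tested by Mann-Whitney on post minus baseline (5.6.1).

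**2. The plan's own figure.** N = 30 / (1 − 0.10) = 33.3, rounded up to 34. This reproduces.

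**3. How many patients could be concerned.** A 10% loss is 0.10 × 34 = 3.4 patients, or 1.7 per arm. At the retention target, 0.80 × 34 = 27.2 complete the study, a loss of 0.20 × 17 = 3.4 per arm. The 10% covers failures of every kind, not only patients who have data and are then left out. A range of 1 to 3 in one arm is therefore an assumption. Three of 17 (17.6%) lies within the loss that the retention target tolerates.

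**4. One patient followed through the text.** A randomised patient has a medication change, the investigator judges it incompatible, and the patient then takes the final examination. Baseline and final FGA both exist. Under 5.4 the patient is a drop-out for the analysis. Under 5.6.1 the patient is analysed as randomised, if counted among the cases analysed. Neither section refers to the other, so two analysts could reach different analysis sets from the same protocol.

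**5. Illustrative size.** If k of n patients in one arm are removed, and each changed D points less than the rest of that arm, the arm's mean change is overstated by k × D / n. With n = 17 and D = 4:

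| k removed | Shift in that arm's mean change (FGA points) |
|---|---|
| 1 | 4/17 = 0.24 |
| 2 | 8/17 = 0.47 |
| 3 | 12/17 = 0.71 |

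If the other arm loses the same number with the same deficit, both means shift equally and the between-arm bias is zero.

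**6. PDQ-39 rules side by side.**

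| Items in scale | Missing items needed for the index (4.4.9.1, literal) | Missing items allowed (Missings) | Both met |
|---|---|---|---|
| 10 | 5 or more | 5 or fewer | only at 5 |
| 6 | 3 or more | 3 or fewer | only at 3 |
| 4 | 2 or more | 2 or fewer | only at 2 |
| 3 | 2 or more | 1 or fewer | never |

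A fully completed questionnaire has 0% missing and fails the 4.4.9.1 condition. Three of the eight dimensions have three items (social support, communication, physical discomfort). The condition applies to all dimensions, so no patient can satisfy both rules.

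**The case against.** The best reply is that the protocol nowhere excludes anyone. Retention is itself a feasibility endpoint and needs a definition of who did not complete; the wording in 5.4 may serve only that. The final examination for early leavers and the continued use of stored data in 6.5 both point towards keeping patients in. The intention-to-treat sentence can also be read as covering all cases, each analysed in the assigned group. This stands to the extent that exclusion is an inference, not stated text. It does not remove the gap: on that wider reading 5.6.1 conflicts with a literal 5.4, and on the narrower one the set is left open.

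A reader might infer more than the documents support:

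- **That patients with a few poor scores are dropped.** The trigger speaks of no interpretable scores. On its plain reading, such a patient has nothing to analyse.
- **That the named tests amount to a complete-case analysis valid only under missing completely at random, and must give way to a likelihood-based model.** The tests do need both values, and the topic of the study is a thin reason for the missingness assumption. But the protocol does not prescribe a complete-case analysis, and handling of missing outcomes may sit in an analysis plan that is not shown. Change-score tests need less than missing completely at random. With one FGA visit after baseline, such a model would add little.
- **That the medication judgement is made with knowledge of the arm.** Section 4.1.4 blinds raters to allocation and participants to the hypotheses. It does not say what the deciding investigator knows.
- **That the PDQ-39 error takes patients out of the intention-to-treat set.** It concerns one secondary index and leaves the FGA untouched. Section 4.4.9.1 also cites scoring syntax and the German scoring instructions, which may prevent the error in practice.

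**Conclusion.** Two separate points hold.

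First, 5.4 and 5.6.1 are not reconciled. Followed literally, 5.4 can remove randomised patients who have outcome data, for reasons linked to disease course, and so bias the primary FGA comparison. The size cannot be known from the documents. The 0.24 to 0.71 points assume that all losses fall in one arm and that each removed patient has a 4-point deficit, a value borrowed from the minimum detectable change and not a documented effect. The figure is also a shift in a mean, whereas FGA is summarised by the median and tested by ranks. It shows direction and order of magnitude, and under balanced loss it vanishes.

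Second, the PDQ-39 index condition is reversed against the protocol's own Missings rule. This is certain and needs no assumption, but it is confined to one secondary score.

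This is a small pilot with inference described as preliminary. The case for correction rests on the ambiguity of the analysis set and the low cost of removing it, not on a demonstrated bias.

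**What to change.** **In 5.4 and 5.6.1:**

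- Define the intention-to-treat set as all randomised patients in their assigned arm.
- State that drop-out status describes retention only and does not remove a patient from the analysis.
- Use all available outcome data, including the early final examination. For patients who withdraw consent, use the data stored up to withdrawal, within the limits of 6.5.
- Treat an uninterpretable score as missing for that variable only.
- Reconcile the medication-change trigger with intention-to-treat by flagging these patients and excluding them only in a sensitivity analysis. This concerns the analysis alone; no change to clinical management is proposed.

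**In 4.4.9.1:** change the condition so that the index needs at least 50% of items answered in every dimension, in line with the Missings paragraph.

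**Cost:** protocol wording only, since the early final examinations are already planned. Patients whose medication changed may dilute the contrast slightly; the sensitivity analysis shows by how much the result depends on them.
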